#### Analysis methods

##### Primary outcome measures

The primary outcome measures will be analysed using logistic regression adjusting for the treatment group and the stratification variables (age group, operator level) as fixed effects and site and patient as random effects (allowing for the same patient to be recruited more than once into the study). A model without adjustment for age group or operator level will also be reported. Unadjusted and adjusted odds ratios (ORs), 95% confidence intervals (CIs) and *p*-values for the adjusted model will be reported (Table 2). Assumptions of the models will be tested and reported on.

**Table 2 Tab2:** Intubation characteristics of participants enrolled in the Kids THRIVE trial

Characteristic	Standard care, *N* =	THRIVE, *N* =
**Intubation location,** *n (%)*		
Emergency department		
Paediatric intensive care		
Neonatal intensive care		
Others		

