### Analysis

#### Outcome definitions

*Intubation attempt* is defined as a single advanced airway manoeuvre beginning with the insertion of the laryngoscope into the child’s mouth and ending when the laryngoscope is removed from the child’s mouth, or where there is a change in operator during the procedure even if the device is not removed.

*Hypoxaemia* is defined as transcutaneous oxygen saturations (SpO_2_) of ≤ 90% or a SpO_2_ saturation difference ≥ 10% for patients with cyanotic congenital heart disease with known substantial right-to-left shunts measured with the bedside monitor and with an accurate quality of the trace during the intubation attempt. Oxygen saturations will continue to be recorded for at least 2 min after the intubation attempt.

A *successful first attempt intubation* is defined as a successful placement of an endotracheal tube at first attempt, without any hypoxemia (SpO_2_ ≤ 90%or saturation difference ≥ 10% for right-to-left shunt). An unsuccessful first attempt intubation is either a successful first attempt intubation associated with hypoxemia, or requirement for more than one intubation attempt.

*Intubation attempt with rescue oxygenation* is defined as the provision of rescue oxygenation (for example, by bag and mask system) following an unsuccessful intubation attempt.

The following are the primary outcomes:

The clinically relevant and patient-centred outcome measures for intubation are hypoxemia and the number of attempts to achieve successful endotracheal intubation, both of which are strongly linked. Therefore, this study has two primary outcomes:Intubation attempt without hypoxaemiaSuccessful first attempt intubation

The following are the secondary outcomes:Number of intubation attemptsNumber of intubation attempts with rescue oxygenationLowest oxygen saturations during each attempt *(intubation attempt as unit of analysis)*

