**Indication for intubation**		
Inadequate oxygenation,* n (%)*		
Inadequate ventilation,* n (%)*		
Unprotected airway,* n (%)*		
Haemodynamic instability,* n (%)*		
Procedure/intervention required,* n (%)*		
Expected clinical deterioration,* n (%)*		
Failed extubation,* n (%)*		
Upper airway obstruction,* n (%)*		
Others,* n (%)*		

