**Pre-intubation observations**		
SpO_2_ * mean (SD)/median (IQR)*		
Hypotension, *n (%)*		
Heart rate centile		
< 10th centile,* n (%)*		
10–90th centile,* n (%)*		
> 90th centile,* n (%)*		
Respiratory rate centile		
< 10th centile,* n (%)*		
10–90th centile, *n (%)*		
> 90th centile,* n (%)*		

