**Subgroup: location of intubation^**					
Emergency department,* n (%)*					
Paediatric intensive care unit,* n (%)*					
Neonatal intensive care unit,* n (%)*					

*IQR* interquartile range, *CI* confidence interval

^*^Adjusted for study site and patient only; *p*-value = xx

^a^Adjusted for age at randomisation, operator level, study site and patient

^*p*-value represents interaction term

We will undertake the following subgroup analyses (Table 2):Age group at randomisation (stratification variable; pre-planned)Operator level (stratification variable; pre-planned)Location of intubation (ED, PICU or NICU; defined after commencement of trial)

All subgroup analyses will examine the primary outcome only. Subgroup analyses will be undertaken using the same analysis methods described for the primary outcome measure, with the addition of the subgroup variable and its related interaction term into the main regression model; the interaction effect (and 95% CI and *p*-value) will be reported, alongside the descriptive statistics for the outcome under investigation. A forest plot will be developed to present heterogeneity between the treatment group and subgroup variable, including the *p*-value, and presented. Additionally, a sensitivity analysis will be undertaken based on the lowest SpO_2_ during intubation (< 80%; ≥ 80%).

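### The primary model leaves out pre-intubation SpO2 and shunt status: the planned test stays valid, but cheap precision and correction of chance imbalance are forgone

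*SAP article*

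**What the plan says.** The Primary outcome measures section specifies "logistic regression adjusting for the treatment group and the stratification variables (age group, operator level) as fixed effects", with site and patient as random effects. The Table 3 footnote confirms the set: "Adjusted for age at randomisation, operator level, study site and patient". A version without age group and operator level is also reported. Neither version contains an oxygenation variable.

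Outcome definitions sets hypoxaemia at SpO2 of 90% or below during the attempt. A change rule applies to one group only: "SpO_2_ saturation difference ≥ 10% for patients with cyanotic congenital heart disease with known substantial right-to-left shunts". The second primary outcome carries the same threshold: "An unsuccessful first attempt intubation is either a successful first attempt intubation associated with hypoxemia, or requirement for more than one intubation attempt".

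The relevant baseline data are already planned. SpO2 is the first row under "Pre-intubation observations" in Table 2, and right-to-left shunt at intubation is a row in Table 1. Table 2 also lists "Inadequate oxygenation" among the indications, so poorly oxygenated children are expected. The Randomisation section stratifies by site, age and operator seniority, not by SpO2.

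**The concern.** For an outcome that is a threshold on SpO2, the child's starting SpO2 is a natural prognostic covariate. Shunt status decides which rule applies. The SAP already accepts that the starting level matters, because it judges cyanotic children by change.

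Two things are at stake. Adjusting for a prognostic baseline variable in a logistic model raises the power of the treatment test, so leaving it out forgoes that gain. And because randomisation does not balance SpO2 by design, only the analysis can correct a chance difference between arms in starting saturation. The one SpO2-based sensitivity analysis, which splits on the lowest value during intubation at 80%, uses a post-randomisation value and cannot do this.

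**Working it through.** **Step 1: reproduce the plan's figures.** Inputs from Sample size and Statistical principles: 16% v 8%, two-sided alpha 0.025, 90% power. Pooled-variance formula for two proportions, per arm:

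n = [z(0.9875)·√(2·p̄·(1−p̄)) + z(0.90)·√(p1(1−p1) + p2(1−p2))]² / (p1−p2)²

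With p̄ = 0.12:
- 2.2414 × √0.2112 = 1.030
- 1.2816 × √0.2080 = 0.584 (0.5845 before rounding)
- (1.030 + 0.5845)² / 0.0064 ≈ 407.3, so 408 per arm and **816** in total, as stated.

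The same formula for 60% v 80% gives 129 per arm, **258** in total, as stated. Attrition: 816 / 0.85 = **960**, as stated. This formula uses no covariates, so the 90% does not depend on adjusting for SpO2.

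**Step 2: what adjustment would add.** The documents give no association between pre-intubation SpO2 and the outcome, so a range is assumed. Trials were simulated with 408 encounters per arm and a standard normal baseline covariate (higher meaning higher risk) with log odds ratio b per SD. Marginal event rates were held at 16% and 8%. Each of 3,000 data sets per row was fitted by logistic regression with and without the covariate, at two-sided alpha 0.025. Site, patient, age and operator effects were left out for simplicity.

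| b per SD (assumed) | AUC of covariate | Power without | Power with | Gain (points) |
|---|---|---|---|---|
| 0 | about 0.5 | 0.909 | 0.908 | none |
| 0.5 | 0.63 | 0.905 | 0.917 | 1.2 |
| 1.0 | 0.74 | 0.904 | 0.934 | 3.0 |
| 1.5 | 0.82 | 0.899 | 0.959 | 6.0 |
| 2.0 | 0.87 | 0.894 | 0.976 | 8.2 |

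The Monte Carlo standard error of one entry is at most about √(0.9 × 0.1 / 3000) = 0.005. Each pair of fits uses the same data sets.

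**Step 3: validity without adjustment.** With no treatment effect (4,000 runs each), the rejection rate without the covariate was 0.025 at b = 1.0 and 0.024 at b = 2.0. With it, the rates were 0.026 and 0.023. Nominal is 0.025.

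**Step 4: chance imbalance in one trial.** The arm difference in mean of a standardised covariate has SD √(1/408 + 1/408) = 0.070, so a difference of 1.96 SDs is 0.137. On the conditional log-odds scale this shifts the comparison by b × 0.137, that is 0.069 at b = 0.5 and 0.274 at b = 2.0. The simulated conditional odds ratios were 0.447 and 0.327, with logs −0.805 and −1.118. The shift is therefore about 9% (0.069/0.805) to 25% (0.274/1.118) of the effect. That is an unlucky draw and not the expected case.

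**The case against.** The strongest reply is that nothing in the plan is wrong. Adjusting for stratification factors, with site and patient as random effects, is conventional and pre-specified. Steps 1 and 3 bear this out: the sample size is correct and the test keeps its level. All of that stands.

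A reader might infer more than the documents support in four ways.
- *That the planned 90% power is missed.* It is not. It comes from an unadjusted formula, and the unadjusted simulations stay at about 0.89 to 0.91. Only a possible gain is forgone.
- *That chance imbalance makes the test invalid.* It does not. The error rate and confidence interval already allow for it. The point concerns the estimate from this one trial.
- *That children at or below 90% beforehand are automatically events.* Hypoxaemia is assessed during the attempt, which begins when the laryngoscope is inserted, and the Intervention section places pre-oxygenation before that. Such a child is an event only if saturation is at or below 90% during the attempt. A listed indication does not show how often that happens.
- *That children who start low erode the power for 16% v 8%.* The documents give no share of such children, and the audited 16% may already include them. That would be a question about the outcome definition or effect size, and covariates would repair it only in part.

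It is also fair that lowest saturation is analysed as a secondary outcome, so conclusions do not rest on the 90% cut alone. That does not replace baseline adjustment.

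**Conclusion.** The point holds as an inexpensive improvement. The plan tabulates pre-intubation SpO2 and shunt status, rests both primary outcomes on saturation, and uses neither variable in the primary model. The planned analysis is valid and its stated power is intact.

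The forgone gain is about 1 to 8 power points at 816 encounters for an assumed AUC of about 0.63 to 0.87, and zero without association. The true association cannot be fixed from the documents. It also depends on when the Table 2 SpO2 is read, which the article does not state; a reading before pre-oxygenation may predict less well than the step is meant to suggest, because pre-oxygenation is intended to change it. The calculation covers hypoxaemia; for first-attempt success the direction is the same, but no size was computed.

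**What to change.** Before unblinding, amend the adjusted primary model as follows and declare the change, as Statistical principles provides.

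- Add pre-intubation SpO2 as a continuous, flexible term (spline or fractional polynomial). Use a reading taken before study therapy starts, and state its time point.
- Add right-to-left shunt status and its interaction with SpO2, because the baselines of cyanotic children sit on another scale and a shared curve would not fit them.
- Keep encounters with missing baseline SpO2 by simple imputation that ignores treatment arm. Otherwise they drop out of the primary model. The Missing data section covers only missing outcomes.
- Keep the currently planned model as a sensitivity analysis.
- Report a standardised risk difference beside the odds ratio, since the odds ratio becomes conditional on SpO2 and moves further from 1 (in the simulation from 0.457 with no association to 0.327 at b = 2.0).
- Any supportive analysis limited to non-cyanotic encounters above 90% must select on that same pre-therapy reading. The Intervention section starts THRIVE before the laryngoscope is introduced, so a reading taken once THRIVE has begun could be affected by allocation.

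The cost is SAP wording and code, plus a check that the recorded SpO2 was taken before study therapy. Both variables are already planned for tabulation. Choosing the same adjustment after unblinding would look data-driven.

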### Sample size

A conservative estimate of the primary outcome of hypoxaemia is set at 16%, following an unpublished 2016 audit of data from the Queensland Children’s Hospital, which we found was comparable to a published report [1]. Assuming a clinically relevant effect size of a 50% reduction in the proportion of desaturation events from 16 to 8%, along with a type I error of 0.025 (adjusting for two primary outcomes using Bonferroni’s correction) and power of 90%, 816 intubation encounters in total are required. Successful first-attempt intubation, the second primary outcome, assumes an absolute increase from 60 to 80%, requiring 258 intubation encounters. Allowing for 15% attrition, the total sample size that will satisfy both primary outcome measures is 960 intubation encounters. An attrition rate of 15% was selected based on the assumption that a proportion of patients enrolled will have a clinical deterioration, or other clinical events, during a high-stress procedure leading to the inability to deliver the intervention or collect the outcome data required for the study.

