### Statistical principles

The primary analysis will be conducted based on the intention-to-treat principle. Specifically, each randomised intubation encounter will be analysed based on the allocated treatment group, independent of compliance with the treatment delivered.

A per-protocol analysis including all intubation attempts where a study therapy was commenced (regardless of whether it was the therapy that was randomised) will also be undertaken and reported in the supplementary material.

The unit of analysis for most outcomes is the intubation encounter. If patients are required to be intubated more than once, they can be re-enrolled and re-randomised, theoretically receiving different study interventions for each intubation attempt within a single admission. For secondary outcomes relating to admission (i.e. ventilator-free days, length of ICU and hospital stay and death), only those patients with one enrolment per admission will be included in the primary and per-protocol analyses.

Statistical tests will be two-sided applying a statistical significance level of 0.05, although the primary outcomes will be analysed at a level of 0.025 (applying Bonferroni’s correction). We will not apply a formal correction for multiple testing to any of the subgroup analyses, sensitivity analyses or to the secondary outcomes. We will ensure conclusions drawn as a result of analyses are interpreted with deference to multiple comparisons.

If there is more than 10% of data missing for the primary outcomes, a sensitivity analysis using multiple imputation will be undertaken.

Continuous variables will be assessed for normality; this will be undertaken using visual inspection of histograms and *Q*-*Q* plots.

Descriptive statistics will be used when summarising variables; frequencies (percentages) for discrete variables, mean and standard deviation (SD) for normally distributed continuous variables, or, if continuous variables are non-normally distributed, median with interquartile range (IQR).

Subgroup analyses will be executed regardless of any potential treatment effect on the primary or secondary outcomes in the main cohort.

Changes to the analysis plan by the investigators effective after the publication of this SAP will be declared as such.

The statistical analysis will be undertaken using StataSE version 17 (StataCorp Pty Ltd., College Station, TX).

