#### Missing data

The primary outcome for this study is recorded by two methods, paper CRF and video recording, as such it is expected that there will be very few participants with missing primary outcome data. Where the data is not recorded on either the paper CRF or video, the medical record will be used to source the required data. As such, multiple imputation will only be undertaken if > 10% of the primary outcome data is unavailable and reported as sensitivity analysis. The fully conditional specification will be used for imputation; the imputation model will include randomised treatment arm, study site and the stratification variable. Ten sets of imputed data will be created using the methods described for the primary outcome. A pooled common effect estimate and 95% confidence interval will be generated from the imputed datasets.

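### The two primary outcomes are tested at 0.025, but their total-cohort odds ratios are to be reported with 95% intervals, which match a 0.05 test

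*SAP article*

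**What the plan says.** Under Statistical principles, the general rule is "Statistical tests will be two-sided applying a statistical significance level of 0.05", with an exception: "the primary outcomes will be analysed at a level of 0.025", by Bonferroni's correction for two primary outcomes. The same section exempts subgroup, sensitivity and secondary analyses from any formal correction. Sample size uses the corrected level too ("along with a type I error of 0.025").

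Under Primary outcome measures, the reporting rule for these outcomes is "Unadjusted and adjusted odds ratios (ORs), 95% confidence intervals (CIs"), with p-values for the adjusted model. The Table 3 shell carries the total-cohort rows and the subgroup rows in the same columns. Both estimate columns are headed with a 95% interval, and a p-value column stands beside them. The Table 3 footnotes describe the adjustment sets and the interaction p-value but do not mention 0.025.

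Nowhere does the SAP give a 97.5% interval for a primary outcome, or say that the 95% intervals are descriptive and that only the p-value decides.

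**The concern.** A two-sided test at level α rejects when the (1 − α) interval excludes the null value. The interval that matches a 0.025 test is therefore 97.5%. With a 95% interval beside it, the main results row can show two answers: an interval that excludes an odds ratio of 1, and a p-value above the pre-specified threshold.

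The layout makes this easy to miss. Total-cohort rows, which are corrected, share columns with subgroup rows, which are not. Secondary outcomes are to be reported without p-values, so a reader of Table 4 has only 95% intervals to go by and may read Table 3 in the same way. At stake is the reading of the main result when the evidence is moderate.

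**Working it through.** **Inputs from the SAP.** Hypoxaemia 16% v 8% ("50% reduction in the proportion of desaturation events from 16 to 8"%); first-attempt success 60% v 80%; level 0.025 per outcome; "power of 90%, 816 intubation encounters in total are required"; 258 encounters for the second outcome; 15% attrition; 960 in total; 1:1 allocation; two primary outcomes.

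**1. Which level did the design use?** Pooled-variance formula for two proportions, no continuity correction, n per arm:

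n = [z(1−α/2)·√(2p̄(1−p̄)) + z(0.90)·√(p₁(1−p₁) + p₂(1−p₂))]² / (p₁ − p₂)²

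- Hypoxaemia, two-sided α = 0.025: [2.2414 × 0.45957 + 1.2816 × 0.45607]² / 0.08² = 407.3, so 408 per arm and 816 in total. This matches.
- First-attempt success, same α: 128.04, so 129 per arm and 258 in total. This matches.
- Attrition: 816 / 0.85 = 960. This matches.
- At two-sided α = 0.05 the totals would be 690 and 218, which do not match.

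Two-sided 0.025 is therefore the operative level in the design as well as in the analysis.

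**2. Width of the matching interval.** Multiplier for 97.5%: 2.2414. Multiplier for 95%: 1.9600. Ratio: 2.2414 / 1.9600 = 1.144, so the matching interval is 14.4% wider on the log odds ratio scale.

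**3. What a mismatch looks like.** Assumed counts, simple unadjusted Wald odds ratio, 408 per arm: 65/408 (15.9%) v 44/408 (10.8%).

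- log OR = −0.4496, SE = 0.2092, z = −2.149, OR = 0.638, p = 0.032.
- 95% interval: 0.423 to 0.961 (excludes 1).
- 97.5% interval: 0.399 to 1.020 (includes 1).

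The test at 0.025 fails, yet the planned interval excludes no effect.

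**4. How often it would occur.** The chance of 0.025 < p < 0.05 is the power at 0.05 minus the power at 0.025, using the same normal approximation. The SAP's 16% control rate is kept. THRIVE-arm rates other than 8% are assumptions.

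| Hypoxaemia, control v THRIVE | 408 per arm | 480 per arm |
|---|---|---|
| 16% v 8% (design) | 0.9416 − 0.9005 = 4.1% | 0.9691 − 0.9435 = 2.6% |
| 16% v 10% | 0.7226 − 0.6210 = 10.2% | 0.7902 − 0.7001 = 9.0% |
| 16% v 11% | 0.5518 − 0.4396 = 11.2% | 0.6208 − 0.5101 = 11.1% |
| 16% v 12% | 0.3768 − 0.2756 = 10.1% | 0.4308 − 0.3241 = 10.7% |

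The 408 column is the number required before the attrition allowance (816/2). The 480 column is full enrolment with no loss (960/2). With no treatment effect the chance is 0.05 − 0.025 = 2.5% per outcome. For first-attempt success at its design effect (60% v 80%) it is below 0.01% with 408 per arm.

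**The case against.** The strongest reply is that error control lies in the test. The test is fixed at 0.025, the adjusted p-value is printed in the same row as the interval, and nothing in the SAP says that success is judged from the interval. A 95% interval is also a valid estimate for each odds ratio taken singly, and a plan may pair a Bonferroni test with 95% intervals if it states their role. All of this stands, and it limits the point to reporting. The SAP does not state that role, however, so the gap remains.

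Two stronger readings are tempting.

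- *Multiplicity control is lost.* If both outcomes were judged from 95% intervals, the family-wise error could reach 0.05 + 0.05 = 0.10 (0.0975 if independent), and joint coverage would be guaranteed only at 90%. But the SAP does not use that decision rule. The figures are also worst-case bounds, and the SAP itself describes the two outcomes as closely linked: first-attempt success requires absence of hypoxaemia.
- *The imputed analysis has the same fault.* The Missing data section says "A pooled common effect estimate and 95% confidence interval will be generated from the imputed datasets". That analysis is designated a sensitivity analysis, and Statistical principles exempts sensitivity analyses from correction, so 95% there agrees with the plan.

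It is also fair to object that the 10–11% figures rest on effects that the SAP does not state, and that the SAP expects little missing outcome data, which favours the 480 column. At the design effect that lowers the chance to 2.6%. At the smaller effects it makes little difference.

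**Conclusion.** The point holds for the total-cohort intention-to-treat results of the two primary outcomes. Their intervals are set at a level that does not match their test, and the SAP does not reconcile the two. The conflict appears only when p falls between 0.025 and 0.05. For hypoxaemia that is a chance of roughly 3–4% at the design effect and 9–11% if the THRIVE-arm rate is 10–12%; for first-attempt success at its design effect it is negligible.

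These chances rest on a simple two-proportion normal approximation, not the planned mixed logistic model, and on a 16% control rate. The mismatch itself depends on neither. The test, its error rate and the figures 816, 258 and 960 need no change. This is an inconsistency in reporting that is worth correcting before results are known.

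**What to change.** - In Primary outcome measures, and in the total-cohort rows of Table 3, report 97.5% intervals for the two primary outcomes in the intention-to-treat analysis, alone or beside 95% intervals.
- Add a Table 3 footnote saying that significance for the primary outcomes is judged at p < 0.025. If 95% intervals are also shown in those rows, say that they are descriptive.
- Keep 95% intervals for subgroup, secondary and sensitivity analyses, including the imputed analysis. Changing those would go against the exemption in Statistical principles. A 97.5% interval for the per-protocol analysis is optional.

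The cost is a few words in the SAP, a confidence-level option in the code, and primary intervals about 14% wider on the log odds ratio scale. No new data and no change to the sample size are needed.
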